### Outcomes {12}

The primary outcome measure will be a change in the symptoms of anxiety and depression, as determined by the RCADS-25-P and RCADS-25-C [28, 29], between study entry (T0) and 1–3 days after the end of the intervention (T1, after five sessions of psychotherapy, five weeks of access to the psychoeducational videos, or both). The RCADS-25-P and RCADS-25-C will be completed by an independent clinician blinded to the allocation, on the basis of interviews (through videoconference or telephone call) with the guardians and the children/adolescents, respectively. The response variables will be the continuous T-scores for the three RCADS-25 domains (total, depression and anxiety).

Secondary outcomes will include the following: a change in the symptoms of anxiety and depression at follow-up; global functioning, assessed by the Clinical Global Impression (CGI) scale [41] and the Children’s Global Assessment Scale (CGAS) [30, 42]; the impact of mental health symptomatology, as determined with the Strengths and Difficulties Questionnaire (SDQ) impact supplement [43]; changes in irritability; emotional problems; environmental changes, as determined by passive smartphone data collection; the level of parental satisfaction with the telepsychotherapy sessions; and the potential harm (emergence of suicidal ideation and worsening of the quality of family relationships).

The blinded assessor will evaluate the difference between the anxiety and depressive symptomatology observed at T0 and that observed at follow-up (T2, 30 days after the last psychotherapy session, for the intervention group, or 30 days after the last video is made available, for the active control group) in an interview with the guardian and the child/adolescent, using the RCADS-25-P and RCADS-25-C.

The blinded assessor will evaluate the global functioning of the participants in interviews with the guardian and the child/adolescent (through videoconference or telephone call). The CGI-Severity (CGI-S) and CGAS scores obtained at T0 will be compared with those obtained at T1 and with those obtained at T2. Scores on the CGI-S range from 1 to 7, higher scores corresponding to greater symptom intensity. Scores on the CGAS range from 0 to 100, higher scores indicating better functionality. The CGI-Improvement (CGI-I) scores will be assessed at T1 and T2. Scores on the CGI-I range from 1 (“very much improved”) to 7 (“very much worse”).

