## Statistical methods

### Statistical methods for primary and secondary outcomes {20a}

We will use generalised linear mixed models (GLMMs) to analyse the effects of the intervention. The primary outcome will be the change, from T0 to T1, in the total scores on the RCADS-25-P and RCADS-25-C. Fixed and random effects will be modelled with GLMMs. The fixed effects will be the randomisation status (intervention group vs. active comparator group) as an independent variable, along with the potential confounders (age, sex and other baseline characteristics). The random effect will be on the subject (first) level. Time will be inserted as a continuous independent variable. We will use the intention-to-treat approach—all randomised subjects will be included in the analysis, even if they drop out or switch arms. The marginal means of the models will be extracted by randomisation status and time, after which they will be plotted in a time series. In a second step, we will analyse the effects that the intervention has on the symptoms of depression and anxiety in the children and adolescents. For all models, we will present the beta coefficients with a confidence interval of 95%. For all statistical tests, the level of significance will be set at 5%. Analyses will be performed with the Stata software package, version 16.0 (StataCorp, College Station, TX, USA), and the programme R, version 4.0.1 (The R Foundation for Statistical Computing, Vienna, Austria).

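### The primary outcome is the change from T0 to T1, but the model described names no randomisation-by-time term and no T1 contrast; fitted as written, its randomisation coefficient averages in the baseline visit

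*Protocol article*

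**What the plan says.** The section on statistical methods for primary and secondary outcomes {20a} sets the target: "The primary outcome will be the change, from T0 to T1, in the total scores on the RCADS-25-P and RCADS-25-C". It then describes the model:

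- Fixed part: "The fixed effects will be the randomisation status (intervention group vs. active comparator group) as an independent variable, along with the potential confounders", these being age, sex and other baseline characteristics.
- Random part: "The random effect will be on the subject (first) level".
- Time: "Time will be inserted as a continuous independent variable".
- Reporting: "For all models, we will present the beta coefficients with a confidence interval of 95" per cent.
- Display: "The marginal means of the models will be extracted by randomisation status and time, after which they will be plotted in a time series".

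The Outcomes section {12} says what is modelled: "The response variables will be the continuous T-scores for the three RCADS-25 domains (total, depression and anxiety"). The response is therefore the score at each visit, not a change score. The same section makes the change from T0 to T2 (the 30-day follow-up) a secondary outcome. No randomisation-by-time term and no between-arm comparison at T1 is named anywhere in the article.

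**The concern.** A treatment effect on change from T0 to T1 is the amount by which the arm difference at T1 exceeds that at T0. In a repeated-measures model with T0 among the responses, that quantity is carried by a randomisation-by-time term. Without one, the model holds the arm difference constant over visits, and the randomisation coefficient is a visit-averaged difference. One of the visits averaged is T0, where randomisation makes the expected difference zero.

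The reported coefficient would then understate the effect on the primary outcome, and a real effect of the planned size could be missed. The plotted marginal means would be parallel lines whatever the data showed. If an interaction was intended, the article leaves open which coefficient or contrast is the primary test.

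**Working it through.** **Inputs.** From Sample size {14}: effect size 0.41, alpha 0.05, power 80%, 1:1 allocation, minimum 190, attrition 30%, total 280. Assumed, because the article gives no figure: between-visit correlation ρ of 0.3, 0.5 or 0.7, equal SD of 1 at each visit, balanced data, no expected difference at T0.

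**The plan's own figure.** A two-sided two-sample t-test with d = 0.41 and 80% power needs 94.35, so 95 per arm and 190 in total, as stated. Then 190/0.7 = 271.4, so 272, against 280 stated, which is close. The sample size is not in dispute. With 280 randomised and 30% lost, 280 × 0.7 = 196 remain, or 98 per arm, used below.

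**What the coefficient estimates without an interaction.** With balanced data it is the arm difference in person means over visits:

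- T0 and T1: (0 + 0.41)/2 = 0.205, or 0.5 of the T1 effect.
- T0, T1 and T2, effect sustained: (0 + 0.41 + 0.41)/3 = 0.273, or 0.67 of it.

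These factors do not depend on ρ.

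**Power.** Power = Φ(effect/SE − 1.96), with SE = √[(2/98) × V]:

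| Quantity tested | Effect | V | ρ = 0.3 | ρ = 0.5 | ρ = 0.7 |
|---|---|---|---|---|---|
| Coefficient as written, two visits | 0.205 | (1+ρ)/2 | 43% | 38% | 34% |
| Coefficient as written, three visits, sustained effect | 0.273 | (1+2ρ)/3 | 75% | 65% | 57% |
| T1 contrast from the interaction, unadjusted | 0.41 | 2(1−ρ) | 68% | 82% | 96% |
| T1 contrast, baseline-adjusted | 0.41 | 1−ρ² | 85% | 91% | 98% |

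Example, two visits at ρ = 0.5: SE = √(0.0204 × 0.75) = 0.124; 0.205/0.124 − 1.96 = −0.30; Φ = 38%.

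A mixed-model simulation at 95 per arm and ρ = 0.5 (300 replicates) gave a two-visit coefficient of 0.21 with 37% rejection, against 0.42 and 83% for the interaction at T1. With three visits it gave 0.29 and 72%, above the closed-form 0.273 and 64%. A check on person means with 20,000 replicates returned 0.273 and 64%, so the excess is simulation error and the closed form stands.

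**Continuous time.** With T0 and T1 only, linear and categorical time are the same model. The form of time matters only if T2 is included and an interaction with linear time is added. Assume visits at weeks 0, 5 and 9.3 and true differences of (0, 1, 1) in units of the T1 effect. Mean time is 4.77, and the squared deviations sum to 43.33. The slope is (0.233 + 4.533)/43.33 = 0.110 per week. The fitted difference at T1 is 0.667 + 0.110 × 0.233 = 0.69 of the truth. The slope-implied T0 to T1 change is 0.110 × 5 = 0.55 of it.

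**The case against.** **An interaction may have been intended.** The article gives no equation, and time appears outside the sentence that lists the fixed effects, so that list is not exhaustive. Marginal means by arm and time make little sense as a plot if the lines are parallel by construction. A fuller model statement may sit in an analysis plan that is not shown. This stands as far as intent goes: a reader might infer that the trial will certainly be analysed without an interaction, and the article does not establish that. It does not remove the point. The article chose to state the terms, the form of time and the reported quantity, and those do not yield the T0 to T1 effect. Marginal means can be taken from an additive model, and no T1 contrast is named.

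**The response might be a change score.** The Outcomes section says T-scores. A change-score model with T1 and T2 rows would still average the T1 effect with T2.

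**Continuous time is not itself the error.** This stands for a model of T0 and T1 alone. The distortion under linear time needs both an added interaction and T2 in the primary model, and the article states neither. Weeks 0, 5 and 9.3 are assumptions.

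**Power is not always worse.** This stands too. At ρ = 0.3 the three-visit coefficient as written has 75%, more than the 68% of the unadjusted T1 contrast. The loss is clear at every assumed correlation with two visits, but not uniform with three.

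**Conclusion.** The point holds as a mismatch between the stated primary outcome and the stated model. Followed literally, the randomisation coefficient estimates half of the T1 effect with two visits, or two thirds with three visits and a sustained effect. Its power is about 34–43% or 57–75% over the assumed correlations, against 80% planned. These factors rest on balanced data and equal expected baselines; missing T1 scores would give T0 more weight and dilute further.

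Two stronger readings are not supported. A reader might infer a risk of false positive findings: averaging in a visit with no expected difference pulls the estimate towards the null and does not inflate type I error. A reader might also infer that linear time by itself invalidates the analysis: it is harmless with T0 and T1 only, and becomes a second problem only with T2 and a linear interaction.

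**What to change.** Amend {20a} to say, in substance: *the mixed model for the RCADS-25 T-score will include randomisation, visit as a categorical factor, the randomisation-by-visit interaction, and age, sex and the other planned baseline characteristics. Baseline will be handled either by a common T0 mean in both arms or by the T0 score as a covariate with T1 and T2 as responses. The between-arm contrast at T1 is the primary test; the contrast at T2 is secondary.* One of the two baseline options should be chosen before the data are seen.

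The interaction and the named contrast are what recover the primary effect. Handling baseline adds precision, which matters if the correlation is low (85% against 68% power at 0.3). The covariance structure can be left to the analysis plan.

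The cost is a change of wording and a few more model parameters. No new data and no change to the sample size are needed.

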### Interim analyses {21b}

There will be no interim analyses.

### Methods for additional analyses (e.g. subgroup analyses) {20b}

Subgroup analyses will be conducted for children and for adolescents, as well as for the participants who were considered completers (i.e. attending three or more sessions) and did not start other mental health treatments (e.g. another psychotherapy intervention or psychotropic medication) during the intervention period.

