**Methods:**

We will conduct a two-arm, parallel randomised controlled trial involving children and adolescents (8–11 and 12–17 years of age, respectively) with symptoms of anxiety, depression or both, according to the 25-item Revised Child Anxiety and Depression Scale (*t*-score > 70). A total of 280 participants will be randomised to the intervention group or the active control group, in a 1:1 ratio. Those in the intervention group will receive five weekly sessions of cognitive-behavioural therapy via teleconference. The sessions will focus on stress responses, family communication, diaphragmatic breathing, emotions, anger management, behavioural activation and cognitive restructuring. Participants in both groups will have access to 15 videos covering the same topics. Participant-guardian pairs will be expected to attend the sessions (intervention group), watch the videos (control group) or both (intervention group only). A blinded assessor will collect data on symptoms of anxiety, depression and irritability, at baseline, at the end of the intervention and 30 days thereafter. Adolescents with access to a smartphone will also be invited to participate in an ecological momentary assessment of emotional problems in the week before and the week after the intervention, as well as in passive data collection from existing smartphone sensors throughout the study.

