### Intervention description {11a}

#### Intervention group

We have developed a brief standardised, manualised cognitive-behavioural intervention for treating anxiety and depression in children and adolescents, to be implemented by trained psychologists via teleconference or telephone call. The main focus of the sessions will be skills training, with a CBT approach that employs vocabulary adapted to the target population. The psychotherapy programme will consist of five structured weekly sessions. The structure of each session is described in detail in the manual. Below is a brief description of the topics covered in each psychotherapy session.Session 1—The initial session covers the following: identification of the main symptoms and problems; psychoeducation on stress responses; strategies for improving communication within the family (e.g. defining minimal routines at home and how parents can listen to their child empathically); and relaxation and mindfulness techniques (diaphragmatic breathing exercises).Session 2—The second session focuses on emotion recognition and anger management. There is a psychoeducational component on emotions, covering the basic emotions of happiness, sadness, fear, disgust, surprise and anger, as well as their usefulness (e.g. motivating us to take necessary actions) and pitfalls (e.g. the potential for suffering). There is a greater emphasis on anger, exploring its physical, cognitive and behavioural components, and on strategies for coping with outbursts of anger, such as how they can be prevented and how to recover from one.Session 3—The third session focuses on behavioural activation, which is a technique based on the idea that avoidance behaviours exacerbate depressive symptoms. The technique is aimed at promoting adaptive behaviours that would be positively reinforced by scheduling potentially enjoyable and meaningful activities [37]. The rationale of behavioural activation is to stimulate participation. The therapist will guide the child/adolescent, with the help of a guardian, in creating a brief list of activities to be performed in the following week.Session 4—The aim of the fourth session is to teach the principles of cognitive restructuring. To that end, there is a psychoeducational component on what “thoughts” are, how to recognise them and the effects they might have on us, covering the basics of the cognitive model developed by Aaron T. Beck [38]. The last part of the session will focus on Socratic questioning [39].Session 5—The final session is aimed at revising any content of the previous sessions that was not clear to the family and providing a referral if necessary (e.g. to the public health care system if the child/adolescent is still symptomatic).

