#### Active control group

Children and adolescents in the active control group will receive a psychoeducational intervention that consists of the same 15 videos described above. The videos will be made available through the same smartphone application and on to the same schedule described for the intervention group.

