### Strategies to improve adherence to interventions {11c}

The intervention sessions will be recorded on video; 10% will be randomly selected to be watched by one of the authors of the manual, to assess therapist adherence to the protocol. Each session is described in detail in the manual, helping make the intervention more homogeneous among the various therapists of the research group. All of the therapists will receive weekly supervisory sessions led by senior psychotherapists. An assessor blinded to the allocation will register the percentage of psychoeducational videos watched by the patient and guardian.

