### Sample size {14}

In a meta-analysis, Vigerland et al. [51] found the estimated size-effect for internet-delivered CBT in children and adolescents to be 0.62 (95% CI 0.41–0.84). Given that most of the studies assessed in that meta-analysis evaluated interventions involving a greater number of sessions than that to be evaluated in our study, we decided to be conservative and expect an effect size within the lower bound of that confidence interval, that is, 0.41. Therefore, the minimum sample size would be 190 participants, with an alpha of 0.05, power of 80% and 1:1 randomisation. Assuming an estimated attrition rate of 30%, we will need a total sample of 280 participants.

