### Methods in analysis to handle protocol non-adherence and any statistical methods to handle missing data {20c}

For the intention-to-treat analysis, we will use GLMMs. We will also perform secondary analyses excluding those not considered completers and those who started any other mental health treatment during the intervention period.

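### The secondary completer analysis rests on session attendance, which children receiving the control intervention cannot meet, so it has either no comparator or one selected arm

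*Protocol article*

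**What the plan says.** All references are to the protocol article.

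- **Completer rule.** Section {20b} lists, beside the analyses for children and for adolescents, an analysis "for the participants who were considered completers (i.e. attending three or more sessions) and did not start other mental health treatments".
- **Use of the rule.** Section {20c} names the intention-to-treat mixed models first and then adds: "We will also perform secondary analyses excluding those not considered completers and those who started any other mental health treatment during the intervention period".
- **Intervention arm.** Under Intervention description {11a}: "The psychotherapy programme will consist of five structured weekly sessions". Families in this arm also have the 15 videos.
- **Control arm.** "Children and adolescents in the active control group will receive a psychoeducational intervention that consists of the same 15 videos described above". No sessions are offered.
- **What each arm is expected to do.** The Methods part of the abstract says: "Participant-guardian pairs will be expected to attend the sessions (intervention group), watch the videos (control group) or both (intervention group only".
- **Adherence recorded in both arms.** Section {11c}: "An assessor blinded to the allocation will register the percentage of psychoeducational videos watched by the patient and guardian". The completer rule makes no use of this.
- **Primary analysis.** Section {20a} is by intention to treat: "all randomised subjects will be included in the analysis, even if they drop out or switch arms".

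**The concern.** A completer rule that only one arm can satisfy does not define a comparison between arms. Someone programming sections {20b} and {20c} must either drop every control or decide, without guidance from the text, that the session rule applies to the intervention arm only. In the second case, children who stayed engaged are compared with all controls, engaged or not. Part of any difference then reflects who keeps attending and not what the sessions do.

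The second criterion has a related problem. Sections {11b} and {11d} connect more intensive care with worsening symptoms, so removing children who start other treatment removes some poor outcomes, possibly at different rates in the two arms.

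The label matters too. Age is a baseline factor that the allocation algorithm balances (section {16a}), whereas completion happens after allocation and depends on it. Listing both as subgroup analyses invites readers to give them the same standing.

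**Working it through.** **1. The plan's own figures.** The sample size section {14} uses an effect of 0.41, alpha 0.05 (taken as two-sided), power 80% and 1:1 allocation. A two-sample t-test needs 94.35, so 95 per arm and 190 in total, which matches the stated 190. For 30% attrition, 190 / 0.70 = 271.4, so 272; the article uses 280, which leaves 280 × 0.70 = 196. The sample size stands. With 280 randomised there are 280 / 2 = 140 per arm.

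**2. The rule set against the content of each arm.**

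| | Intervention | Control |
|---|---|---|
| Sessions offered | 5 | 0 |
| Videos offered | 15 | 15 |
| Can attend at least 3 sessions | yes | no |
| Can start other treatment | yes | yes |

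- *Literal reading:* controls retained = 0 of 140. No between-arm estimate exists.
- *Session rule applied to the intervention arm only:* with completion share c, 140 × c children are compared with 140 controls, before the other-treatment exclusion.

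**3. Size under the second reading, simple form.** Let g be the gap in outcome between completers and non-completers that would exist whatever the treatment. The whole-arm mean is c × (completer mean) + (1 − c) × (non-completer mean). Hence completer mean − whole-arm mean = (1 − c) × g. The article gives neither c nor g. Assuming 1 − c = 0.30 and g = 0.3 to 0.5 SD:

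- 0.30 × 0.3 = 0.09 SD, and 0.09 / 0.41 = 22% of the planned effect;
- 0.30 × 0.5 = 0.15 SD, and 0.15 / 0.41 = 37%.

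**4. Size under wider assumptions.** Suppose there is no true effect and completion is the upper share c of a normal latent variable that has correlation rho with the outcome. Then bias = rho × φ(z) / c, where z is the (1 − c) quantile and φ the normal density. The standard error is √(1/(140c) + 1/140).

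| c | rho | Bias (SD) | Share of 0.41 | Two-sided rejection rate (nominal 5%) |
|---|---|---|---|---|
| 0.9 | 0.1 | 0.019 | 5% | 5.3% |
| 0.7 | 0.3 | 0.149 | 36% | 20.5% |
| 0.6 | 0.5 | 0.322 | 79% | 64.5% |

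Over c = 0.6 to 0.9 and rho = 0.1 to 0.5, the bias runs from about 0.02 to 0.32 SD.

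**5. Adding the other-treatment exclusion.** Let shares f_I and f_C of the two arms start other treatment, and let these children do worse by g_I and g_C. Ignoring overlap with the session rule, excluding them shifts the contrast towards the intervention by f_I × g_I − f_C × g_C. The article gives none of these four quantities, so the sign is open. If more controls start other treatment, the shift runs against the session filter in step 3.

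**The case against.** The best defence is that this is a supplementary analysis behind a properly stated intention-to-treat primary, that section {20c} openly calls it an exclusion, and that a small wording change using the recorded video percentage would close the gap. The first two points stand and limit the weight of the finding. The third is a workable fallback, but it yields only a defined non-randomised comparison.

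Several stronger statements are tempting, and the article does not support them.

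- *That the completer analysis is the only method for non-adherence.* Section {20c} names the intention-to-treat models first. Section {18b} collects T1 and T2 outcomes however many sessions were attended or videos watched.
- *That 30% is the non-completion rate.* Section {14} gives it as attrition for the whole sample, and the Discussion as dropout in psychotherapy trials generally. Neither is the share attending fewer than three sessions. If controls also drop out, the controls analysed are themselves selected, and step 3 may overstate the bias.
- *That the completer effect will exceed the intention-to-treat effect.* The session filter alone plausibly favours the intervention, but step 5 shows that the combined rule has no known direction.

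The remedy is also open to challenge. A complier-average estimate with a three-session cut assumes that one or two sessions do nothing, although section {11a} places breathing exercises, family communication and anger management in sessions 1 and 2. Suppose 30% are non-completers, all attend one or two sessions, and they obtain half the benefit e. The intention-to-treat effect is then 0.70e + 0.30 × 0.5e = 0.85e, and 0.85e / 0.70 = 1.21e, about 21% too large (0.09 SD if e = 0.41). That objection stands: the assumption must be stated and the cut varied. Section {20a} also foresees arm switching, so one-sided non-compliance is expected but not guaranteed.

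**Conclusion.** The point holds for the secondary completer analysis only. The article fixes a definition that children receiving the control intervention cannot meet, so this is a stated rule that fails and not a detail left to an analysis plan. A rare control who switches arms and attends sessions does not rescue it. The other-treatment criterion adds post-randomisation selection in both arms with no predictable net direction.

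The figures in steps 3 and 4 of the working show that the bias could matter beside the planned effect. They are not estimates for this trial, because completion rate, prognostic gap and correlation are all assumed. A reader might infer that the trial's main conclusion is at risk; it is not, since the intention-to-treat analysis and the sample size are untouched. The change should be made because it is cheap and because the analysis cannot be interpreted as written.

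**What to change.** In sections {20b} and {20c}:

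1. Replace the completer exclusion with a complier-average causal effect estimate: randomisation as the instrument, receipt defined as attending at least three sessions, the same covariates as the primary model, and all randomised participants kept.
2. State its limits. It is less precise than the intention-to-treat estimate. It assumes that one or two sessions have no effect and is too large if they do, so repeat it with another cut, for example any session, as a sensitivity analysis. Count any control who switches and attends sessions as having received them.
3. Report starts of other mental health treatment by arm and do not exclude those participants.
4. If a completer analysis is still wanted, define adherence in both arms: sessions for the intervention arm, the recorded percentage of videos watched for controls. Label it an exploratory, non-randomised comparison and not a subgroup analysis.

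The cost is revised wording and one extra model with a sensitivity run. No new data are needed: outcomes are collected regardless of adherence (section {18b}), other treatment is recorded from T0 to T2 (section {22}), and videos watched are registered (section {11c}).
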